#### Macro-level: primary and secondary outcomes

Analyses of primary (research question 1) and secondary outcomes (research questions 3–7) on the macro-level will be carried out using generalized linear mixed modeling (LMM). For ratio scale endpoints or if distributions of endpoints are skewed, robust LMM is used. Separate models are run for each endpoint. Fixed factors are condition (intervention/control), time (pretest/posttest/follow-up), and the interaction effect of condition*time. Random intercepts are fitted at the participant level. The pretest value of the endpoint is included as a control variable. In a secondary sensitivity analysis, we will also include parental gender, parental age, child age, EMA participation (yes/no), trauma type (interpersonal/non-interpersonal), child exposure to trauma (no trauma exposure/co-exposed to parental trauma/exposed to trauma separate from the parental trauma), and number of comorbid psychiatric diagnoses of the parent as covariates.

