### Study design

This study uses a two-arm randomized controlled trial (RCT) design: the intervention condition receives KopOpOuders-PTSD in addition to TAU and is compared to a control condition which only receives TAU. This design allows us to test whether the effect of KopOpOuders-PTSD in addition to TAU is superior to that of TAU only. The randomization ratio is 1:1. Block randomization (2:4:6) is used, stratified by the Arkin Mental Health Care department (Sinai Centrum or other; clients of Sinai Centrum have PTSD as their primary diagnosis, whereas clients of other departments typically do not) to ensure even distribution across conditions. Double-blind randomization is not possible, because participants and prevention professionals providing in-person sessions know automatically whether the participant is receiving the intervention. Therefore, we apply single blinding, in which the researcher overseeing the assessments and analyzing the results is blind to the condition. Randomization is done by a research assistant who is not involved in the assessments. Randomization outcomes are only accessible to this research assistant. Participants are instructed not to share their randomization outcome with the researcher overseeing their assessments, and professionals carrying out the intervention are instructed not to discuss any identifying details of intervention participants with the researcher. Unblinding is possible if needed in case of (serious) adverse events, and can be done by the primary investigator, who is not involved in assessments. To ensure parenting support is not withheld due to participation in this study, control condition participants are invited to complete the online KopOpOuders-PTSD modules after their participation and will receive information about the parenting support options at Arkin Mental Health Care.

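### Randomization is stratified by department, but department is in neither the primary macro-level model nor the sensitivity covariates; adding it is a small, conditional and nearly free gain in precision

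*Protocol article*

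**What the plan says.** Under Study design, the protocol article states "The randomization ratio is 1:1" and "Block randomization (2:4:6) is used", "stratified by the Arkin Mental Health Care department (Sinai Centrum or other"). It explains that "clients of Sinai Centrum have PTSD as their primary diagnosis, whereas clients of other departments typically do not". The stated purpose is an even spread of departments over the two conditions.

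Under Macro-level: primary and secondary outcomes, the model is spelled out: "Fixed factors are condition (intervention/control), time (pretest/posttest/follow-up), and the interaction effect of condition*time". It continues "Random intercepts are fitted at the participant level", and the pretest value of the endpoint is a control variable. A second model is also listed term by term: "In a secondary sensitivity analysis, we will also include parental gender, parental age, child age, EMA participation (yes/no), trauma type (interpersonal/non-interpersonal"), followed by child trauma exposure and number of comorbid psychiatric diagnoses, seven covariates in all.

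Department is in neither list. The EMA model (Micro-level: primary endpoint) and the moderation models do not name it either, and no section says that the analysis will reflect the stratification.

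**The concern.** Balancing the arms on a factor that predicts the outcome lowers the true variance of the treatment estimate. A model without that factor leaves its variance in the error term, so the reported standard error does not reflect the gain. Intervals then cover more than 95%, the test rejects less than 5% of the time under the null, and some power is given up.

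This cannot be put down to an article condensing a longer plan. The article names every term of the primary model and goes as far as a seven-item covariate list. That list includes EMA participation but leaves out the one factor the design itself balances on. Comorbidity count is at best a partial proxy, because it does not show which diagnosis is primary.

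**Working it through.** **1. The plan's own figure.** Inputs from Sample size: d = 0.55, power 0.80, two-sided alpha .05. A two-sample t-test needs 52.87, so 53 per condition (power 0.801 at 53). Then 53/0.75 = 70.7, so 71 per condition and N = 142. The figure reproduces and does not depend on department.

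**2. General size for one between-person comparison.** Let R² be the share of residual variance, after the pretest score, that department explains. The documents do not give it; 0 to 0.10 is assumed. With arms balanced within department:

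- SE without department / SE with department = 1/√(1−R²)
- type I error without department = 2·[1 − Φ(1.96/√(1−R²))]
- with SE₀ = √(2/53) = 0.194, power without department = Φ((0.55 − 1.96·SE₀)/(SE₀·√(1−R²))), and with it = Φ(0.55/(SE₀·√(1−R²)) − 1.96)

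| R² (assumed) | SE ratio | Type I error without | Power without | Power with |
|---|---|---|---|---|
| 0 | 1.000 | 0.050 | 0.808 | 0.808 |
| 0.02 | 1.010 | 0.048 | 0.811 | 0.816 |
| 0.05 | 1.026 | 0.044 | 0.814 | 0.828 |
| 0.10 | 1.054 | 0.039 | 0.821 | 0.847 |

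The base power is 0.808 rather than 0.801 because these formulas use the normal approximation. The gain from adding department is 0.816 − 0.811 = 0.5 points up to 0.847 − 0.821 = 2.6 points.

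**3. What the pretest covariate already absorbs.** Assume total SD 1 without department, correlation 0.6 between visits and 60% of participants at Sinai Centrum. The posttest variance left after pretest is 1 − 0.6² = 0.64. A 0.5 SD department difference adds variance 0.6 × 0.4 × 0.5² = 0.06.

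- *Difference present at every visit.* Variance becomes 1.06 and covariance with pretest 0.66. Left after pretest: 1.06 − 0.66²/1.06 = 0.649. SE ratio √(0.649/0.64) = 1.007.
- *Difference arising only after pretest.* Left after pretest: 0.64 + 0.06 = 0.70. SE ratio √(0.70/0.64) = 1.046.

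**4. The model as written.** The mixed model was simulated with three visits, condition, time, their interaction, pretest covariate and participant intercept. Settings: 106 participants with complete data, the same assumed correlation and department split, blocks of 2, 4 and 6 within department. SE without department divided by SE with a department main effect:

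| Department difference | Posttest contrast, model as written | Posttest contrast, post-baseline outcomes only | Condition-by-time contrast |
|---|---|---|---|
| 0.5 SD, stable | about 1.005 | about 1.007 | 1.000 |
| 0.8 SD, stable | about 1.01 | about 1.015 | 1.000 |
| 0.5 SD, after pretest only | about 1.03 | about 1.04-1.05 | 1.000 |

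The last column follows from the structure. Department is constant within a participant, so its main effect shifts all visits alike and cancels from a difference of changes. In that setting a department-by-time term recovered about 2% when the difference arose after pretest.

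**The case against.** The strongest case against the point is that the consequence is close to nil under the stated model. Three parts of it stand.

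- The relevant quantity is what department explains after the pretest score, and the plan already adjusts for pretest. The documents give no figure; if department adds nothing, nothing is lost.
- The macro-level analysis section does not say which contrast is tested. If it is condition by time, a department main effect changes nothing. H1, however, is worded as a difference between conditions at posttest, and for that contrast department can matter.
- The error runs in the safe direction. The estimate is not biased, and a positive result would stand.

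A reader might infer more: that the trial's intervals are certainly too wide, that stratifying was wasted, or that power would rise from 0.80 to about 0.84. The documents do not support this. The excess width depends on an unknown R². The stated purpose of stratifying, balance between arms, is kept. The power gain must be counted from the stratified but unadjusted analysis, which is already slightly above nominal power when department is prognostic.

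A reader might also extend the point to the EMA and moderation analyses. EMA participation is optional and randomization is not stratified by it, so balance by department within that subset is not guaranteed. The moderation test concerns condition by PCL-5 score, a different contrast. No gain has been shown for either.

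The objection does not remove the omission itself. Both covariate lists are explicit, and the stratification factor is in neither.

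**Conclusion.** The point holds in a small, conditional form. The trial stratifies by department and plans to analyse without it. If department predicts the outcome beyond the pretest score, the model-based standard error of the posttest difference is too large by roughly 0-1% for stable department differences (about 1.5% for a 0.8 SD difference when only post-baseline outcomes are modelled). It is too large by about 3-5% if a 0.5 SD difference arises after pretest. These sizes rest on an assumed correlation of 0.6 between visits, an assumed 60% share from Sinai Centrum and assumed department differences; none of these is in the documents.

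The result is a mildly conservative test, with no bias and no inflated type I error. No conclusion of the trial is threatened. The reason to act is that the gain is nearly free, and that settling the covariate in advance avoids a later choice between adjusted and unadjusted results.

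**What to change.** Add department (Sinai Centrum or other) as a fixed effect in the primary and secondary macro-level models, and carry it into the sensitivity model. State that the treatment effect is the between-arm difference at posttest, and likewise at follow-up, adjusted for the pretest value and department. That contrast matches H1 and is the one to which the gain applies. Adding department to the EMA and moderation models for consistency is harmless, but no gain should be claimed there.

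The cost is one degree of freedom per model. The stratum must be known for every participant before randomization, so no further data collection is needed and N stays at 142. The change should be recorded before the allocation is unblinded for analysis.

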#### Expansion to blended care

The three minimal contact moments were replaced by three 90-minute in-person sessions with a preventive mental health professional. To uphold the emphasis on parental autonomy and self-direction while instituting more extensive contact with a professional, the role of the professional is that of ‘facilitator’ rather than ‘leader’. All professionals receive a 12-hour training, and sessions are carried out according to a manual to ensure consistency. Whereas the content of the online modules remains largely the same as in the original KopOpOuders Self-Help-intervention (and thus applicable to a wide range of mental health and addiction problems), the in-person sessions have a more in-depth and PTSD-specific focus. In the sessions, parents receive psychoeducation about PTSD and parenting, are encouraged to ask for individualized guidance, and get the opportunity to practice newly learned skills. In-person sessions are carried out one-on-one, but parents are encouraged to bring a partner or other significant person in the final session.

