### Participants

#### Sample size

We assumed a medium effect size for the primary macro-level outcome (parenting behavior: Alabama Parenting Questionnaire), *d* = 0.55, based on RCTs with similar designs, interventions and populations as the current study, and with the same primary outcome [21, 82]. With a power of 0.80 and significance level of *p* = .05, the minimum *n* is 53 per condition. From previous experience with intervention studies in adults with PTSD, we expect 20–25% dropout. We therefore corrected with 25% oversampling, resulting in 53/0.75 = *n* = 71 per condition, total *N* = 142.

For the primary micro-level outcome (parenting behavior: Short Parenting Scale for EMA), power was calculated using PowerAnalysisIL [83] using our best estimation of relevant parameters. Based on existing EMA literature [84], we assume participants will respond to 70% of the 42 EMA prompts, resulting in 29 complete data points per participant. Assuming an autocorrelation between measurement occasions of *r =* 0.30 and a medium effect size, minimum sufficient power to detect intervention effects would be reached if *n =* 32 (16 per condition) agreed to take part in the EMA component of the study.

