#### Adherence and compliance monitoring

To accurately interpret intervention effects, documenting treatment adherence and compliance in participants and prevention professionals is important. Participants’ adherence is monitored in three ways: completion of online modules and use of PTSD-specific content in the online library (monitored automatically by the intervention platform software), and attendance of in-person sessions (recorded by the prevention professional leading the sessions). In prevention professionals, implementation fidelity is promoted and monitored through mandatory training and monthly intervision sessions with the research team. In each intervision session, a research team member will capture factors affecting intervention fidelity through implementation logs. These implementation logs will be used to identify where guidance and feedback is needed in the intervision sessions. Furthermore, they will be thematically analyzed and described in an implementation report after completion of the study.

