### Analysis

Primary analyses will be conducted on the entire randomized sample (i.e., intention to treat). Extra analyses for comparison will be conducted on the per protocol/treatment completers sample. Participants in the intervention condition who have completed at least six out of eight intervention modules/sessions will be characterized as treatment completers. Participants who fail to complete the intervention, but do not choose to drop out of the study, will complete the posttest and follow-up assessments as normal. Hypothesis testing will be two-sided with an alpha level of .05. Missing data will be handled using multiple imputation (R package MICE or equivalent).

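### Parents in the intervention arm probably share prevention professionals, but neither the macro-level model nor the sample size allows for this; a partially nested sensitivity analysis would be a cheap safeguard.

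*Protocol article*

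**What the plan says.** The protocol article, under Expansion to blended care, says of the adapted intervention: "The three minimal contact moments were replaced by three 90-minute in-person sessions with a preventive mental health professional". The sessions are one-on-one and follow a manual, the professionals receive 12 hours of training, and parents can ask for guidance suited to their own situation. Under Adherence and compliance monitoring, "implementation fidelity is promoted and monitored through mandatory training and monthly intervision sessions with the research team". The Study design section gives the control arm treatment as usual only, so controls have no prevention professional.

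The macro-level model has fixed effects for condition, time and their interaction, with the pretest value as a control variable. Its random part is given in one sentence: "Random intercepts are fitted at the participant level". The covariate list for the sensitivity analysis does not include the professional. The micro-level (EMA) model also has participant intercepts only.

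The Sample size section assumes d = "0.55, based on RCTs with similar designs, interventions and populations as the current study", states "With a power of 0.80 and significance level of" .05, and finds that the minimum n "is 53 per condition". Because "we expect 20–25% dropout", this is raised to 71 per condition. No allowance for clustering is mentioned.

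**The concern.** The design is partially nested: one arm may be grouped by professional and the other is not. Each intervention parent is offered 3 × 90 minutes = 4.5 hours with a professional, in the part of the programme that is most specific to PTSD and most adapted to the individual. If some professionals achieve better results than others, outcomes within a caseload are positively correlated. A participant intercept accounts for repeated measures on one parent, not for correlation between parents of the same professional. A professional effect arises after pretest, so adjusting for the pretest value does not remove it.

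At stake is the precision claimed for the condition effect. If the correlation exists, the interval is too narrow and the test rejects too often. The Dissemination policy section foresees offering the intervention to other institutions if it is found effective. The inference would then have to carry over to other professionals, and this is where variation between them counts as uncertainty.

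**Working it through.** **Inputs from the protocol article.** d = 0.55 with SD set to 1, two-sided alpha 0.05, power 0.80, 53 evaluable per condition, 25% dropout, 1:1 allocation.

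**Inputs assumed, because the article does not give them.** Number of professionals k = 4 to 15, equal caseloads m = 53/k, and professional-level ICC 0 to 0.10.

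**The plan's own figure.** A two-sample t-test with these inputs needs 52.87, rounded up to 53 per condition (power 0.801 at 53). Then 53/0.75 = 70.67, rounded up to 71. Both figures reproduce under independence, so no clustering allowance is built in.

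**Formulas**, with clustering in the intervention arm only and a normal approximation:
- Design effect in that arm: DE = 1 + (m − 1) × ICC
- Naive SE = √(2/53) = 0.1943; true SE = √((DE + 1)/53)
- Type I error of the planned test = 2 × [1 − Φ(1.96 × naive SE / true SE)]
- Power of a test that uses the true SE = Φ(0.55 / true SE − 1.96)

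**Results.** Each cell gives the type I error of the planned test, then the power of a test using the true SE. These are properties of two different tests.

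| k (m) | ICC 0 | ICC 0.01 | ICC 0.02 | ICC 0.05 | ICC 0.10 |
|---|---|---|---|---|---|
| 15 (3.5) | 5.0%; 0.81 | 5.1%; 0.80 | 5.3%; 0.80 | 5.7%; 0.78 | 6.5%; 0.76 |
| 8 (6.6) | 5.0%; 0.81 | 5.3%; 0.80 | 5.7%; 0.79 | 6.6%; 0.76 | 8.3%; 0.71 |
| 4 (13.2) | 5.0%; 0.81 | 5.7%; 0.78 | 6.4%; 0.76 | 8.6%; 0.70 | 12.3%; 0.61 |

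The ICC 0 column shows 0.81 rather than 0.80 because the normal approximation gives 0.808 at 53 per arm.

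**One case in full: 9 parents per professional, ICC 0.05.**
- DE = 1 + 8 × 0.05 = 1.40
- True SE = √(2.40/53) = 0.2128; ratio = 0.2128/0.1943 = 1.095
- The true SE is 9.5% larger than the naive one; equivalently, the naive SE is 1 − 1/1.095 = 8.7% too small.
- Planned test: 1.96/1.095 = 1.79, so type I error is about 0.074. Its power is Φ((0.55 − 1.96 × 0.1943)/0.2128) = Φ(0.795), about 0.787.
- Test using the true SE: Φ(0.55/0.2128 − 1.96) = Φ(0.625), so power is about 0.73.

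All of this describes an unadjusted comparison of 53 per arm, as in the sample size section. The planned model adjusts for pretest and uses repeated measures, so the figures illustrate the effect and do not predict it.

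**The case against.** The strongest reply is that the documents do not establish any clustering. They give no number of professionals, no caseload and no ICC, and they nowhere say that one professional sees several parents. The design also points to a small ICC: sessions are individual and manualised, professionals are trained and meet monthly, their role is to facilitate rather than lead, and only three of the eight components are delivered in person. Under intention to treat, parents who attend few sessions would dilute any professional effect further. If inference is limited to the professionals who took part, variation between them is not missing sampling error. Finally, a random effect estimated from a handful of professionals in one arm is imprecise and may be estimated at zero.

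Most of this stands. It limits the size of the problem and argues against changing the primary model. A reader might infer that the planned standard errors are definitely too small, or that the planned test both over-rejects and falls to a power of 0.73. The documents do not support the first, since it needs a positive ICC and shared caseloads. The second mixes two tests: 0.074 is the planned test's type I error, while 0.73 is the power of a test with the corrected SE.

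Two things remain. Training, a manual and monthly meetings reduce variation between professionals without ensuring that there is none. The implementation logs will describe factors that affect fidelity, but they do not show whether outcomes differ by professional.

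**Conclusion.** The point holds as a conditional one, and acting on it is a cheap improvement. The stated model and sample size assume independence, while the design allows clustering in one arm only. The standard error of the between-arm contrast may be too small if three things are true: professionals see several parents each (inferred, not stated), the professional-level ICC is above zero, and the result is meant to reach other professionals.

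The size depends on two quantities that the documents do not give. Across 4 to 15 professionals and an ICC of 0.01 to 0.10, the planned test's type I error is about 5.1% to 12.3%. The upper end needs both few professionals and a high ICC, which the delivery format makes less likely. With 8 or more professionals and an ICC of 0.01 to 0.02, it stays at or below about 5.7%, which would rarely change a conclusion. At an ICC of 0 the planned analysis is correct.

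**What to change.** Keep the primary model and the sample size. Then:
- Record which professional saw each intervention participant. The professional leading the sessions already records attendance, so the identifier should be obtainable from those records.
- Report the number of professionals and their caseloads with the results.
- Pre-specify a sensitivity analysis of the macro-level outcomes using a partially nested model: a random effect for professional in the intervention arm only, with small-sample degrees of freedom.
- Run it after the blinded primary analysis. The Study design section keeps the analysing researcher blind to condition, and an identifier that exists in one arm only reveals allocation, so it must be withheld until that analysis is complete.

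The cost is one identifier and one additional model. Intervals in the sensitivity analysis will be somewhat wider, and with few professionals the variance estimate will be imprecise. If the model cannot be fitted, say so and report the caseloads.

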### Aims of this study

#### Primary objective

To test the effect of KopOpOuders-PTSD on macro- and micro-level parenting behavior by answering the following research questions:What is the effect of KopOpOuders-PTSD on macro-level parenting behavior?

H1. We hypothesize that parenting behavior at posttest will be more adaptive in the intervention condition than in the control condition. This effect is hypothesized to remain stable at follow-up.2.What is the effect of KopOpOuders-PTSD on micro-level parenting behavior?

H2. We hypothesize that micro-level parenting behavior will be significantly more adaptive at posttest in the intervention condition than in the control condition.

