### Instruments

#### Primary outcomes

##### Macro-level: parenting behavior

Parenting behavior is measured using the Dutch translation of the caregiver-reported Alabama Parenting Questionnaire (APQ [86, 87]). The APQ is a 42-item questionnaire with five subscales: positive involvement with children, supervision/monitoring, use of positive discipline techniques, consistency in discipline techniques, and use of corporal punishment. Items describe parenting behaviors and situations (e.g., ‘You don’t tell your child where you are going’), which are scored for frequency on a five-point Likert scale ranging from ‘never’ (1) to ‘always’ (5). APQ total scores range from 42 to 210. However, subscales are often analyzed separately, with higher scores reflecting higher parenting skills on the ‘positive involvement’ and ‘positive discipline techniques’ subscales, and lower parenting skills on the other three subscales. In this study, we will use the total score as the primary outcome for the main analysis (research question 1) and perform additional analyses on the separate subscales. The APQ has good psychometric properties, with adequate to good internal consistency [88, 89] good test-retest reliability [90] and good construct validity [88, 89].

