#### Macro-level: moderation analysis

To test whether treatment outcomes on macro-level endpoints at posttest are moderated by parental PTSD symptoms at pretest (research question 8), we modify the models for macro-level endpoints by using only the posttest measure of each endpoint and including the moderator variable (PCL-5 total score). Hypothesis 8 is tested using the interaction effect of condition*PCL-5 total score on posttest measurements of the endpoint, while controlling for pretest measurements of the endpoint. A separate moderation model will be run for each endpoint.

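### The macro-level model uses the pretest score both as an outcome and as a covariate, which makes the standard error of the posttest difference between conditions too small

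*Protocol article*

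**What the plan says.** In the protocol article, Macro-level: primary and secondary outcomes, one mixed model is set for each endpoint:

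- Fixed part: "Fixed factors are condition (intervention/control), time (pretest/posttest/follow-up), and the interaction effect of condition*time". Pretest is thus one of the modelled outcome occasions.
- Random part: "Random intercepts are fitted at the participant level". No other within-person structure is given.
- Covariate: "The pretest value of the endpoint is included as a control variable".

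The section does not say which term answers research question 1. The hypothesis itself is a posttest comparison of arms: "We hypothesize that parenting behavior at posttest will be more adaptive in the intervention condition than in the control condition", with the effect expected to persist at follow-up. H3 to H7 have the same form. Under Analysis: "Hypothesis testing will be two-sided with an alpha level of .05".

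**The concern.** On pretest rows the outcome and the covariate are the same number, so the regression slope there is 1. On posttest and follow-up rows the slope is the correlation with pretest (equal variances). The model fits one slope to all rows, so the slope is too steep for the later rows and the pretest residuals are artificially small. The random intercept must describe pretest, posttest and follow-up residuals together, and its variance comes out much too low. The estimated posttest difference remains unbiased under randomization, but its model-based standard error is too small.

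The model serves the primary macro-level endpoint (the Alabama Parenting Questionnaire total) and all five secondary endpoints. A positive posttest result could be challenged for an inflated false-positive rate.

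**Working it through.** **Plan's own figure.** Sample size states: "We assumed a medium effect size for the primary macro-level outcome (parenting behavior: Alabama Parenting Questionnaire), *d* = 0.55", power 0.80, two-sided .05. An unadjusted two-sample t-test with d = 0.55 and 53 per arm has power 0.801 (52 per arm: 0.793), and 53/0.75 = 70.7, so 71. The stated sample size reproduces. I use 53 analysed per arm.

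**Assumptions.** The documents give no correlations between weeks 0, 10 and 22, so these are assumed. Also assumed: equal variances (set to 1), complete data, a Gaussian model and no true effect.

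**Equal correlation r** (the structure that a random intercept itself implies). Per-person variances:

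- fitted covariate slope g = (1 + 2r)/3
- estimated random-intercept variance = (1 − r)(4r − 1)/9; residual variance = 1 − r
- model-based variance of the posttest contrast = the sum of those two
- true variance of that contrast = 1 + g² − 2gr
- type I error = 2Φ(−1.96 × √(model/true))

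| r | g | random-intercept variance | model variance | true variance | SE ratio | type I error |
|---|---|---|---|---|---|---|
| 0.3 | 0.533 | 0.016 | 0.716 | 0.964 | 0.861 | 9.1% |
| 0.5 | 0.667 | 0.056 | 0.556 | 0.778 | 0.845 | 9.8% |
| 0.7 | 0.800 | 0.060 | 0.360 | 0.520 | 0.832 | 10.3% |

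For comparison, the posttest–follow-up covariance given pretest is r − r², which is 0.21, 0.25 and 0.21. The double use leaves only 0.016, 0.056 and 0.060. At r = 0.5 and 53 per arm the model SE is √(2 × 0.556/53) = 0.145, and the true SE is √(2 × 0.778/53) = 0.171.

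Simulation (20,000 trials, 53 per arm) gave 9.3%, 9.9% and 10.3% for r = 0.3, 0.5 and 0.7, and 11.0% for r = 0.8. ANCOVA on posttest alone gave 5.0%, 5.0% and 4.8% for the first three. A standard mixed-model routine (400 trials, r = 0.6) gave 11.5%.

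**Decaying correlations.** Let r̄ be the mean of the three correlations. Then g = (1 + r(pre,post) + r(pre,fu))/3, and the model variance is (1 + 2r̄)/3 − g² + 2(1 − r̄)/3. The true variance is 1 + g² − 2g·r(pre,post) at posttest; at follow-up, r(pre,fu) replaces r(pre,post).

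For 0.7/0.6/0.7 (pre–post/pre–follow-up/post–follow-up): g = 0.767, model variance 0.412, true variance 0.514 at posttest and 0.668 at follow-up.

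| pattern | posttest | follow-up |
|---|---|---|
| 0.7/0.6/0.7 | 7.9% | 12.4% |
| 0.6/0.5/0.7 | 8.3% | 11.5% |
| 0.7/0.5/0.7 | 6.2% | 13.7% |
| 0.8/0.64/0.8 | 5.7% | 14.8% |

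**Condition-by-time term instead.** The covariate is constant within a person, so it drops out of the pretest-to-posttest contrast. Model variance is 2(1 − r̄) and true variance is 2(1 − r(pre,post)). Under equal correlation these agree and the error is 5.0%. In the four decaying patterns it is 3.9%, 5.0%, 3.0% and 2.7%. It rises to about 7% only where posttest and follow-up correlate more strongly with each other than either does with pretest (0.5/0.5/0.7: 6.8%). Power at d = 0.55 with 53 per arm is that of a change-score t-test: 0.66, 0.80 and 0.95 for r = 0.3, 0.5 and 0.7. For ANCOVA, with variance 1 − r², it is 0.84, 0.90 and 0.98.

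**The case against.** The strongest reply is that the section never names the tested contrast. It lists the condition-by-time interaction, a conventional test in a model with pretest, posttest and follow-up, and that term is close to nominal at posttest. This stands as far as it goes: a reader might infer that the primary test simply runs at 9 to 11%, and the documents do not support so flat a statement. But the hypotheses are worded as posttest differences, and the parallel micro-level section says that differences between conditions at posttest are analysed. The reading that inflates the error is therefore a natural one. On the other reading, the covariate does nothing for the test.

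Second, the 9 to 11% needs equal correlations across 22 weeks. With decay the posttest figure is lower. That is right, but the error then moves to follow-up, where effects are also claimed.

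Third, multiple imputation and the robust model for skewed endpoints were not included, so the figures show direction and rough size, not the trial's actual error rate.

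Fourth, lower power than ANCOVA is no error in itself. The interaction term meets the planned 0.80 at r = 0.5 and above, and falls short only at the lower correlation tried.

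A reader might also infer that the moderation model is broken, because it would keep a random intercept with one record per participant: "we modify the models for macro-level endpoints by using only the posttest measure of each endpoint". The document does not say that the random intercept is kept. As written, that section describes a posttest model controlling for pretest, which is sound, so no criticism is made of it.

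**Conclusion.** The double use of the pretest score is stated in the text; it is not a detail left to an analysis plan. It gives a standard error that is 14 to 17% too small for the posttest difference between conditions under equal correlations of 0.3 to 0.7, and a type I error of about 9 to 11% for that contrast. Under decaying correlations the error is about 6 to 8% at posttest and about 12 to 15% at follow-up. These figures rest on assumed correlations, complete Gaussian data and 53 per arm, and apply only if the between-condition difference is what is tested. If the condition-by-time term is tested, the posttest error is roughly 3 to 5% in the same settings, and the pretest covariate has no effect on the test. A general claim that the false-positive rate is doubled is not supported. That the model as written gives wrong standard errors for the hypotheses as worded is supported.

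**What to change.** Use the pretest once. Either of these works:

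1. Model only posttest and follow-up as outcomes, with condition, time, condition-by-time and the pretest score as covariate. A pretest-by-time term and an unstructured covariance between the two occasions are preferable but not essential: with a random intercept alone, this model had a type I error of 4.9 to 5.4% under equal correlation (2.9 to 5.5% over all patterns tried).
2. Keep pretest as an outcome, constrain the two arms to a common baseline mean, and drop the pretest covariate.

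In either case, name the adjusted between-condition difference at posttest as the primary contrast and the difference at follow-up as secondary. The cost is a few words in the analysis section and a few lines of code. No new data are needed.
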